### Termination of carriage

All study participants who are nasally colonised with pneumococcus serotype 6B at the end of the study will be asked to take oral amoxicillin 500mg three times daily for 3 days. This dose is based on our UK experience where there have been no attributable SAEs for CHIM in >1500 participants completing the programme This will be communicated at visit G, or by telephone in the unlikely event of only visit G samples (day 14 – see
Table 1) showing carriage.

### Immunological assays

•    
**Antibody titres:** measurement of pneumococcal-specific protein and polysaccharide antibodies will be conducted on nasal wash, salivary and serum samples using ELISA as previously reported
^
21
^. This will allow us to identify potential antibody correlates of protection against pneumococcal colonisation.

•    
**Cellular responses:** measurement of pneumococcal-specific memory B and T cells will be performed on peripheral blood and nasal samples using flow cytometry and ELISPOT as previously reported
^
22,
23
^. This will allow us to identify potential cellular correlates of protection against pneumococcal colonisation. 

•    
**Cytokine profiles:** measurement of cytokines will be done on nasosorption and serum samples using multiplex bead array as previously reported
^
24
^. This will enable us to identify potential soluble marker correlates of protection against pneumococcal colonisation.

•    
**Host transcriptomic analysis:** measurement of host nasal mucosa transcriptomic profile will be done using RNA sequencing (RNAseq) on nasal cells and peripheral blood as previously reported
^
22
^. This will allow us to characterise potential nasal or blood transcriptomic signatures associated with protection or susceptibility to pneumococcal carriage.

•    
**Microbiome profiles:** characterisation of microbial communities will be done on throat swabs and nasal washes using next-generation sequencing and metagenomic analysis as previously reported
^
24
^.

Assays will be harmonised with LSTM standard operating procedures where possible to facilitate comparability between CHIM studies

### Sample size justification

The primary endpoint is the occurrence of pneumococcal colonisation determined by the presence of pneumococcus in nasal wash samples at any time point post inoculation detected using classical microbiology. Secondary endpoints will include density and duration of pneumococcal carriage in nasal wash.

Based on the pneumococcal dose of 80,000 cfu/naris and using data from our feasibility study
^
7,
8
^ and Liverpool-based studies
^
6
^, we estimate that 60% of the control (normal saline) group will be colonised with pneumococci following inoculation and 36% of the PCV-13 group, this equates to a 40% reduction in colonisation. We observed a 78% reduction in the UK based study
^
6
^. However, as Malawian data demonstrates decreased efficacy for PCV-13 in carriage reduction
^
10
^, we have powered the study at approximately half of this effect size. Based on these parameters, we will randomise 67 participants per arm for 80% at a 5% significance level (see
Table 2). To correct for any potential drop out, we will randomise 70 participants to each arm (total 140 participants for primary outcome).

**Table 2. T2:** Power calculations for PCV13 study.

Number per group	Carriage rate control	Carriage rate PCV-13 vaccine	PCV-13 carriage rate reduction	Power
**67**	0.6	0.45	0.25	0.41
**67**	0.6	0.42	0.30	0.55
**67**	0.6	0.39	0.35	0.69
**67**	0.6	0.36	0.40	0.80
**67**	0.6	0.33	0.45	0.89
**67**	0.6	0.30	0.50	0.95

An additional 40 participants will be randomised (1:1, PCV13 vs. normal saline) at the 20,000 pneumococcal dose. A further 20 participants will be randomised (1:1, PCV13 vs. normal saline) at the 160,000 pneumococcal challenge dose. These doses will be used to explore the effects of differential pneumococcal exposure on PCV-13 vaccine efficacy. Recent methodological developments in vaccine efficacy estimation highlight important gains derived from the use of multiple-dose over single-dose experimental designs
^
25
^. By extending our core experiment with smaller groups of participants at doses below and above 80,000 CFU, we will be in a position to not only apply the new methods to a human system for the first time, but also test their performance against a previously established mathematical model
^
25
^. Participant consent is required before screening procedures can be conducted. Any participant who consents but is subsequently determined to be ineligible will be replaced so that a total of 200 participants will be inoculated with
*Streptococcus pneumoniae* for the first phase of the study. Important secondary endpoints including the immune responses, in particular humoral and cellular responses, will also be assessed. Immunological parameters will be compared between pre-vaccination and pre-inoculation values in paired analyses using parametric or non-parametric tests as appropriate.

### Analysis plan

Phase one and phase two of this study will be analysed separately. The reporting of this study will be prepared in accordance to the CONSORT 2010
^
26
^ guidelines. A CONSORT diagram will summarise participant screening, enrolment, randomisation, inoculation, withdrawals, follow-ups and analysis. All continuous data variables will be summarized using the following descriptive statistics: N (size of relevant analysis population), n (size of analysis population without missing values), mean, standard deviation, median, 25
^th^ percentile value, 75
^th^ percentile value and interquartile range, minimum and maximum. The proportion of observed levels will be reported for all binary and categorical measures. When appropriate, corresponding exact, binomial 95% confidence intervals for proportions will be included.

The primary endpoint is the occurrence of pneumococcal colonisation determined by the presence of pneumococcus in nasal wash samples at any time point post inoculation detected using classical microbiology. Secondary endpoints will include density and duration of pneumococcus in nasal wash. While 140 participants will be randomised (1:1, PCV13 vs. normal saline) at the 80,000 CFU pneumococcal dose, an additional 40 participants will be randomised (1:1, PCV13 vs. normal saline) at the 20,000 pneumococcal dose and a further 20 participants will be randomised (1:1, PCV13 vs. normal saline) at the 160,000 pneumococcal challenge dose.

The primary endpoint will be analysed using generalised linear models (GLMs; log-binomial or, in case of convergence issues, logistic regression) with treatment as a single predictor, generating risk ratios and odds ratios together with their 95% confidence intervals of being colonized with pneumococcus between the PCV13 and normal saline control groups. We will use longitudinal data analysis methods, specifically generalised linear mixed models (GLMM) or generalised estimating equations (GEE), to analysis pneumococcal carriage status and density at individual time points with treatment, time and interaction between time and treatment as fixed effects and study participant as random effect / clustering variable.

Immunological parameters will be compared between PCV13 and placebo recipients, as well as between carriers and non-carriers using similar methods (GLMs for comparing parameters according to overall carriage status and/or treatment, GLMMS/GEEs for longitudinal analyses). The area under the curve (AUC) of pneumococcal colonization at days 2, 7 and 14 post inoculation will be calculated using the trapezoidal rule and the AUC will be analysed using a GLM with a single factor for treatment.

The effects of differential pneumococcal exposure on PCV-13 vaccine efficacy will be analysed using recent methodology developed by our team
^
25
^. Expanding vaccine efficacy estimation with dynamic models fitted to cross-sectional prevalence data post-licensure. All quantitative analyses will be conducted in the intention-to-treat population. Analyses will be conducted using the R environment for statistical programming and computing (v4.0.0 or higher). All computer code will be made publicly available on GitHub under a CC BY 4.0 license.

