### Study endpoints

**
*Primary endpoint:*
** detection of the inoculated pneumococci by classical culture methods, at any time point, from nasal wash recovered from the participants at days 2, 7 and 14 following the initial pneumococcal challenge.

**
*Secondary endpoints:*
** Pneumococcal carriage density and duration will also be measured to inform the primary endpoint. Innate, humoral and cellular responses to pneumococcal colonisation will be assessed by immunological assays on collected samples. These data will allow us to define the host variables that predict colonisation and protection due to PCV-13 vaccination.

**
*Social science evaluation:*
** An exit questionnaire (
*Extended data*
^
17
^) will be conducted as part of visit G and visit L to monitor participant satisfaction and acceptability of the study and procedures. Purposeful sampling will be conducted on a subset of individuals to explore acceptability in more detail. This work will focus on perceptions of and concerns about controlled human infection; experience of engagement activities and consent processes; and participant recommendations for future research.

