^. This is a well-used and validated technique to collect nasal bacterial specimens used successfully during our feasibility study. Briefly, 5ml of sterile saline is instilled and held for a few seconds in the nares before being expelled into a sterile Galli pot. This is repeated twice in each naris using 20ml saline in total. In the event of nasal wash loss (defined as cough/sneeze/swallow), the procedure may then be repeated to obtain an adequate specimen. Should the nasal wash reveal natural colonisation of pneumococcus, the participant will continue in the study and receive the inoculation as per protocol, unless the natural serotype is identified as 6B, in which case the participant will be excluded from the study prior to inoculation (primary outcome cannot be determined). All pneumococcal carriage negative participants will continue in the study.

•     
**Nasal cells** will be collected using a nano-sampling method in which cells are obtained through minimally invasive superficial nasal scrape biopsies (Rhino-Pro Nasal Curette, Morphew Curettes). Experience from our feasibility study
^
7
^ demonstrates that participants can be biopsied multiple times with no significant side effects. Nasal cell samples will be obtained after nasal wash samples have been taken. Up to 4 samples (2 per nostril) will be obtained at each nasal sampling visit. If the researcher finds that the sample is insufficient, for example no cells are visible on the rhinoprobe, the sample can be repeated immediately. The rhinoprobes are placed in transport media immediately after collection.

•     
**Throat swabs** will be performed by simple posterior pharyngeal swabbing on a dry swab and placed into culture media. This test will be used to determine infection with SARS-CoV-2 by viral PCR prior to inoculation as part of screening and stored for batch classical microbiological testing (data not used for screening).

•     
**Saliva** will be collected by a salivette held for saturation or a spit in the tube.

•     
**Urine sample** will be taken for a pregnancy test as part of the safety screening. 

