### Determination of colonisation

Colonisation will be defined by the microbiology result of nasal washes taken at 2-, 7- and 14-days post inoculation. Nasal washes will be plated on to culture media and incubated overnight at 37°C in 5% carbon dioxide (CO
_2_). Colonies will be confirmed as
*S. pneumoniae* using classical microbiological techniques including (i) typical draughtsman-like colony morphology, (ii) the presence of α-haemolysis, (iii) optochin sensitivity and (iv) bile solubility. Typing by latex agglutination will be done using a commercial kit to confirm pneumococcal serogroup. Isolates will be frozen at -80
^o^C for storage. Results from the cultured nasal wash will also be confirmed using PCR based methods of bacterial detection.

Monitoring of colonisation will be performed by microbiology analysis of nasal washes. This will include measurement of pneumococcal density by LytA PCR. Monitoring for COVID-19 co-infection will be performed by RT-qPCR analysis of throat swab samples

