### Safety considerations and assessment

**
*Study design to ensure safety.*
** Safety is paramount in human infection studies. While the risk to individuals of developing any infection is very low (40% Malawian adults experience natural colonisation at any time, and the incidence of invasive disease is 20/100 000 patient years
^
28
^), the study is designed to ensure any risk is minimal by appropriate:

•Study team selection and rigorous training in human challenge procedures•Study design with staggered recruitment approach (sample size and dose)•Careful serotype selection, demonstration of safety and acceptability in our feasibility study and 10 years of pneumococcal controlled human infection experience at LSTM•Participant selection and exclusion criteria as detailed○Including exclusion of COVID-19 positive participants at screening visit and continued monitoring for infection at day 2, 7 and 14 after inoculation•Participant education through a participant information sheet (provided)•Rigorous safety procedures including daily monitoring and providing participants with a thermometer and a course of amoxicillin tablets in case of emergency•24-hour emergency telephone contact with researchers, including close individual daily monitoring, and access to hospital facilities and prompt treatment if required•To further mitigate risk, participants will be provided with accommodation for three nights immediately following nasal challenge. If a participant determines that it is not possible to stay at study accommodation for three nights then a pragmatic approach to further study procedures will be taken. If the participant can demonstrate that they remain readily available by phone and accessible with transport, this need not affect the procedure. Twice daily checks could replace the resident period. In the Liverpool CHIM there is no resident period at all. If, however, the participant absconds or is intending to be uncontactable, then participation in the study will be stopped and antibiotics offered as at the end of the protocol.

We will schedule inoculations such that visit G is completed for each pneumococcal dose group (20,000 and 80,000) before progression to the next group (80,000 and 160,000 respectively).

The research investigators have successfully worked together to safely deliver our pneumococcal CHIM feasibility study in Malawi based on knowledge and experience from the Liverpool studies
^
7

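### The primary endpoint is worded in two incompatible ways: inoculated serotype 6B in some sections, any pneumococcus in the sample size and analysis sections

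*Protocol article*

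**What the plan says.** The strain-specific definition is in Study endpoints, where the primary endpoint is "detection of the inoculated pneumococci by classical culture methods, at any time point" in the day 2, 7 and 14 nasal washes. The Abstract agrees. Study design says culture determines colonisation with serotype 6B at each time point.

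The strain-free definition appears twice. Sample size justification has colonisation "determined by the presence of pneumococcus in nasal wash samples at any time point post inoculation", and the Analysis plan has "pneumococcal colonisation determined by the presence of pneumococcus in nasal wash samples at any time point post inoculation detected using classical microbiology". The Analysis plan then names treatment as the only predictor in the primary model.

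Four other statements bear on the difference:
- Screening and preliminary assessment: "Should the nasal wash reveal natural colonisation of pneumococcus, the participant will continue in the study and receive the inoculation as per protocol". Carriers of 6B are the exception and are excluded. The exclusion criteria give the reason: with natural 6B carriage the primary outcome could not be determined.
- Safety considerations and assessment: "40% Malawian adults experience natural colonisation at any time".
- Determination of colonisation, on typing: "Typing by latex agglutination will be done using a commercial kit to confirm pneumococcal serogroup". PCR-based confirmation is also planned, without saying whether it separates serotypes.
- The same section, on monitoring of colonisation: "This will include measurement of pneumococcal density by LytA PCR".

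**The concern.** The primary event has two definitions, and the looser one stands in the section an analyst would program from. In a trial without natural carriers the two would coincide. Here they do not. A participant who carries another serotype and never acquires the challenge strain is a non-event under Study endpoints and an event under the Analysis plan.

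If the looser wording were applied, events unrelated to the challenge would enter both arms and the risk ratio would move towards 1. The direction matters because the main objective is to compare protection in Malawi with that seen in the UK, and the protocol expects a smaller effect in Malawi. Dilution by natural carriage would look like reduced vaccine efficacy.

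Two related gaps remain under the 6B definition. Typing is described only to serogroup, whereas the visit C exclusion and the endpoint need the serotype. LytA PCR density in a retained natural carrier does not isolate the challenge strain, so density, and any AUC built on it, would include the natural strain.

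**Working it through.** **Inputs.** Sample size justification gives control 0.60, PCV13 0.36, and "we will randomise 67 participants per arm for 80% at a 5% significance level", with 70 per arm randomised. The test's sidedness is not stated. Natural carriage of 40% comes from Safety considerations and assessment. It covers all serotypes, so it is used as the top of a range and not as an estimate.

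**1. The plan's own figure.** Pooled two-proportion test, two-sided 5%, no continuity correction, p̄ = mean of the two risks:

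power = Φ{ [ |p1−p2|·√n − 1.96·√(2p̄(1−p̄)) ] / √(p1(1−p1) + p2(1−p2)) }

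With n = 67, p1 = 0.60, p2 = 0.36, p̄ = 0.48: (0.24 × 8.185 − 1.96 × 0.7065) / 0.6859 = 0.845, so power is 0.801. All six rows of Table 2 reproduce to within 0.5 percentage points. At 70 per arm power is 0.818. Under the 6B definition the stated power is therefore right.

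**2. The strain-free wording taken literally.** Let q be the share with natural non-6B carriage found in at least one wash, assumed equal in both arms and independent of 6B uptake. Each risk p becomes p′ = q + (1−q)p. At q = 0.40, control is 0.40 + 0.60 × 0.60 = 0.760 and PCV13 is 0.40 + 0.60 × 0.36 = 0.616.

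| q | Control | PCV13 | RR | Power, 67 per arm |
|---|---|---|---|---|
| 0 | 0.600 | 0.360 | 0.60 | 80% |
| 5% | 0.620 | 0.392 | 0.63 | 76% |
| 10% | 0.640 | 0.424 | 0.66 | 71% |
| 20% | 0.680 | 0.488 | 0.72 | 62% |
| 30% | 0.720 | 0.552 | 0.77 | 53% |
| 40% | 0.760 | 0.616 | 0.81 | 44% |

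At q = 40%, power at 70 per arm is 45%, and 162 per arm would be needed for 80%.

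**3. If PCV13 also lowers natural carriage.** With q = 40% in the control arm and an assumed 10%, 20% or 40% relative reduction of it in the PCV13 arm, power at 67 per arm is 56%, 67% or 85%. In the last case power is not lost, but the apparent reduction in carriage is still 32% instead of 40%, and it mixes two effects.

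**4. Effect on the UK comparison.** Suppose PCV13 reduced 6B carriage by the UK figure of 78%, from the 60% control rate: 0.60 × 0.22 = 0.132. At q = 40% the strain-free score gives 0.40 + 0.60 × 0.132 = 0.479 against 0.760, an apparent reduction of 37%. At q = 20% it is 55% (0.306 against 0.680), and at q = 10% it is 66% (0.219 against 0.640).

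**5. Which definition the planning rates fit.** The Introduction reports the feasibility results as carriage after inoculation with 6B. An any-pneumococcus rate of 36% in the PCV13 arm would also lie below the 40% quoted for natural carriage alone. The 60% and 36% are 6B rates.

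**The case against.** The strongest reply is that the intent is plain. The formal definition stands under the endpoint heading, the Abstract and Study design agree with it, and excluding natural 6B carriers while keeping other carriers makes sense only if other serotypes are not events. Isolates are typed, which an any-pneumococcus endpoint would not need. The sample size and analysis sections never say that other serotypes count, so their sentence can be read as shorthand. This stands as evidence of intent. It does not remove the contradiction, because both sections purport to state the primary endpoint, and the Analysis plan is where the model is specified.

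A reader might go further and infer that the trial does score any pneumococcus and has lost its power. The documents do not support that. The loss arises only if the strain-free sentence overrides Study endpoints.

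Nor is 44% an estimate for this trial. The 40% behind it is an all-serotype figure for Malawian adults, quoted for safety context, and includes 6B carriers, who are excluded here. The exclusions also remove regular and recent smokers, people recently on antibiotics and close contacts of children under 5.

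It is also fair to say that laboratory detail on serotyping is commonly left out of an article, and that LytA PCR is not named as the only source for density. Those two points therefore call for clarification. A particular assay rule for density, or an added any-pneumococcus outcome, would be a matter of preference.

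**Conclusion.** The contradiction is real and concerns the primary endpoint, so it should be corrected before unblinding. The protocol places unblinding after microbiology reporting for the last participant at visit G. Under the inoculated-strain definition nothing is lost: power is 80% at 67 per arm. Applied literally, the strain-free wording would cost between about 4 points of power (5% natural carriage) and about 37 points (40%), with the risk ratio moving from 0.60 to between 0.63 and 0.81.

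These figures assume that natural non-6B carriage is the same in both arms and independent of 6B uptake. Its true level in this population is not given. The loss shrinks, and could vanish, if PCV13 also reduces natural carriage. The conclusion is that two definitions need aligning, with a conditional risk of dilution. It is not that the trial is underpowered.

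**What to change.** 1. In Sample size justification and Analysis plan, replace the presence of pneumococcus with culture of the inoculated *S. pneumoniae* serotype 6B at day 2, 7 or 14, and state that other serotypes are not events.
2. In Determination of colonisation, reconcile typing to serogroup with the serotype 6B requirement in Study design, the exclusion criteria and the nasal wash paragraph, by saying how 6B is distinguished within serogroup 6.
3. State that the density, duration and AUC analyses refer to 6B, and how LytA PCR results are to be read in participants who carry another strain.

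The cost is wording in three sections plus confirmatory typing of serogroup 6 isolates. Post-inoculation isolates are already to be frozen, so that typing can follow later. For the visit C exclusion it must be finished before inoculation, and Table 1 places visit C in week 5 and inoculation in week 6. The sample size does not change.

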### Social science analytical plan

The social science evaluation requires qualitative data to understand volunteer perspectives of benefits, challenges, tolerability of study procedures, and any potential unintended effects through the study. All participants will be asked to complete an exit questionnaire upon completion of visit G (and visit L if consented for the second phase of the study) (
*Extended data*
^
27
^). This questionnaire will be completed by the participant on a tablet computer. Any participant who expresses concern(s) or dissatisfaction will be offered the opportunity to discuss in more detail as part of a semi-structured exit interview conducted as a separate appointment.

In the event that there are several structured exit interviews, all data collected will be audio-recorded and transferred to a qualitative data analysis software package (NVIVO), to enable analysis. Data will be analysed following broad deductively defined themes and inductively derived sub-themes. We will employ a combination of thematic coding in NVivo and use of frameworks to compare perspectives between different stakeholders (participants and study team members). Two researchers will undertake initial coding of an initial small number of transcripts, and then discuss and agree themes for further coding in the event that there are any further transcripts. Analysis will be on-going during fieldwork, using an iterative approach to identify emerging themes that can be clarified or explored further through later data collection. Data will be triangulated between methods and participant groups to cross-check information and provide a more comprehensive analysis. At this point, given responses in the feasibility study, we consider it unlikely that there will be a significant volume of exit interview material to analyse.

